### Analysis

Tests of potential differences across study groups on demographic and clinical history variables were performed by means of analysis of covariance (ANCOVA) for continuous measures and Pearson χ^2 ^for categorical variables. Every analysis conducted using the SPSS software (SPSS 12.0KO for Windows^©^), and performed among two randomised (acupuncture, and waitlist) groups and their stratified (treatment naive, and conventional therapy) sub-groups. The primary analysis will compare outcomes for each primary and secondary outcome measure among the groups to estimate treatment effect with 95% confidence interval (CI). An intention-to-treat (ITT) analysis will be undertaken of the 3-week and 6-week (respectively 9-week and 12-week) data from the K-ADHD-RS, due to some participants who commence the study but do not complete.

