### Primary outcome measures

The primary outcomes for the study were changes in ADHD symptoms from baseline to week 6 (or from week 6-12) as measured by the K-ADHD-RS [38]. The K-ADHD-RS is an 18-item standardized, valid, reliable instrument for the diagnosis and also a weekly assessment tool for checking the of treatment response among children and adolescents with ADHD [39]. Each item on the instrument describes one of the symptoms of ADHD rated on a 0-3 point Likert scale (0 = never or rarely, 1 = sometimes, 2 = often, and 3 = very often) [39]. The principal investigator administered the K-ADHD-RS to the parent at each study visit. Nationally representative norms are available for the scale and were used to determine eligibility [39].

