### Randomization and treatment allocation

This study is designed as a waitlist controlled open trial. Eligible participants were randomly allocated to one of two groups: group A (acupuncture) and group W (waitlist). In each group, participants were stratified according to the pharmacologic intervention at the initiation of the study. A computer generated randomization scheme was used. The principal investigator generated the random allocation sequences without any notice to sub-investigators. Stratified randomization was performed as a separate randomization procedure within each of two subsets of participants (without pharmacologic intervention, 1-60; with pharmacologic intervention, D1-D40. Other treatments were not concerned.) by using block size "4". Each number and its randomised letter (A or W) were placed in an opaque envelope. Each envelope was numbered consecutively from 1-60 and D1-D40. As each parent called to have their child screened, they were allocated the next consecutive number once they were eligible, so that for each eligible participant, no. 1 was allocated to envelope no. 1, etc. The screener was unaware of the sequence of group allocation at the time of screening phase. Hence, allocation was concealed at the time of recruiting.

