### Sample size justification

Sample size calculations are performed to determine the number of participants needed to detect effect sizes similar to those that have been reported in recent ADHD medication trials [56]. This study is powered to detect a 7.04 difference between the groups. A sample size of 32 per group is required to achieve 80% power with a 2-tailed significance level of .05, assuming an equivalent standard deviation of 9.9 in both groups. Estimating a 20% dropout during the study, a minimum of 80 total participants are needed to reach the target 32 participants per group [, μ_c _- μ_t_: Mean difference = 7.04, σ^2 ^= Assumed Common Variance of both treatment and control group (Standard Deviation = 9.9), n = 32]

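### ANCOVA is named only for baseline difference tests; naming it for the treatment effect, with baseline K-ADHD-RS and medication stratum as covariates, would gain precision at no cost

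*Protocol article*

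**What the plan says.** All references are to the protocol article.

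- **Baseline variables (Analysis).** Tests of group differences on "demographic and clinical history variables were performed by means of analysis of covariance (ANCOVA) for continuous measures", with Pearson chi-square for categorical ones. No covariate is named for this ANCOVA.
- **Treatment effect (Analysis).** "The primary analysis will compare outcomes for each primary and secondary outcome measure among the groups to estimate treatment effect with 95% confidence interval". No test, model or covariate is given.
- **Use of the strata (Analysis).** Every analysis is "performed among two randomised (acupuncture, and waitlist) groups and their stratified (treatment naive, and conventional therapy) sub-groups". No pooled estimate adjusted for stratum is mentioned.
- **Primary outcome (Primary outcome measures).** "The primary outcomes for the study were changes in ADHD symptoms from baseline to week 6", on the K-ADHD-RS.
- **Randomisation (Randomization and treatment allocation).** "participants were stratified according to the pharmacologic intervention at the initiation of the study", with blocks of 4 and separate envelope series 1-60 (no medication) and D1-D40 (medication).
- **Sample size (Sample size justification).** A difference of 7.04 points, 80% power, two-sided 5% level, 32 per group, "assuming an equivalent standard deviation of 9.9 in both groups". The text does not say whether 9.9 is the SD of the score or of the change.

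**The concern.** If allocation was sound, any difference between the groups in demographic or history variables is due to chance. A significance test of such a difference therefore answers no useful question. ANCOVA would be of use for the treatment effect, and there the article does not name it.

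A change score accounts for baseline by subtraction, which fixes the slope of week-6 score on baseline at 1. When the true slope is below 1, a group that starts higher by chance tends to fall further through regression to the mean, and the change-score difference moves with that imbalance. ANCOVA estimates the slope instead.

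The stratum is in a similar position. The trial balances on medication status, but the analysis uses it to split the sample and states no pooled estimate that adjusts for it. What is at stake is precision, and protection against chance imbalance, in a trial of 80 children. Validity is not at stake.

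**Working it through.** **Inputs from the article:** difference 7.04, SD 9.9, two-sided 5%, 80% power, 32 per group, 20% dropout, 80 in total.

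**Assumed, because the article does not give them:** the correlation r between baseline and week-6 K-ADHD-RS (0.3, 0.5 and 0.7 shown), equal variances at the two times, and the share of variance explained by the stratum.

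**1. The plan's own figure.** n = 2 × [9.9 × (1.960 + 0.842) / 7.04]² = 31.04, rounded up to 32 per group. 32 / 0.8 = 40 per group, 80 in total. Both reproduce. Standardised difference: 7.04 / 9.9 = 0.711. Power of the two-sample t-test at 32 per group is 80.0% (81.2% by the normal approximation). Half-width of the 95% interval: 1.96 × 9.9 × √(2/32) = 4.85 points. No covariate adjustment enters this calculation.

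**2. Baseline adjustment at 32 per group.** The residual SD depends on what 9.9 is:

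- score SD: 9.9 × √(1 − r²)
- change SD: 9.9 × √((1 + r)/2)

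Power is from the t-test; half-width = 1.96 × residual SD × √(2/32).

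| r (assumed) | If score SD: residual SD | power | half-width | If change SD: residual SD | power | half-width |
|---|---|---|---|---|---|---|
| 0.3 | 9.44 | 84% | 4.63 | 7.98 | 93% | 3.91 |
| 0.5 | 8.57 | 90% | 4.20 | 8.57 | 90% | 4.20 |
| 0.7 | 7.07 | 98% | 3.46 | 9.13 | 86% | 4.47 |

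Every row improves on 80% and 4.85. The two readings agree at r = 0.5 and run in opposite directions on either side of it.

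**3. Comparator.** The 80% applies to whichever quantity has SD 9.9. If that is the week-6 score, the SD of the change is 9.9 × √(2(1 − r)) = 11.71, 9.90 and 7.67, and a change-score comparison has about 66, 80 and 95% power (half-width 5.74, 4.85 and 3.76). ANCOVA is still better in each case. Relative to a change score its variance saving is (1 − r)/2: 35% at r = 0.3, 25% at 0.5 and 15% at 0.7.

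**4. Stratum.** If it explains 2, 5 or 10% of the variance, the residual SD is 9.9 × √(1 − share) = 9.80, 9.65 or 9.39, and power is about 81, 82 or 84%. That is a gain of roughly 1 to 4 points over 80%.

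**5. Splitting instead of adjusting.** If 64 completers divide 60:40 between the strata (assumed), there are about 19 and 13 per arm. Power for 7.04 points is then about 57% and 41% within the strata, so sub-group results cannot stand in for a pooled adjusted estimate.

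**The case against.** The strongest reply is that the article is a condensed account and does not name the model for the treatment effect at all. It neither prescribes nor rules out adjustment, and a fuller protocol or SAP may specify it. An unadjusted sample size does not prove an unadjusted analysis, since planning without covariates and then adjusting is common and conservative. This stands. A reader might infer that the plan commits to an unadjusted comparison, but the documents do not say so.

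A reader might also infer that baseline score and stratum play no part in the treatment comparison. That is wrong: baseline enters by subtraction through the change score, and the strata enter as sub-groups.

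Nor do the documents support a fixed size for the loss. Both r and the meaning of 9.9 are open, and whether the gain grows or shrinks with r depends on the second. That medication status is a strong predictor is not documented either.

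Finally, a comparison without covariates is valid and, after stratified randomisation, tends if anything to be conservative. This also stands, so no claim of bias or inflated error can be made.

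What the reply does not remove is the one use of ANCOVA that the article does fix, on baseline tests, and the better use available for data the trial already collects.

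**Conclusion.** The point holds as a free improvement, not as an error that threatens the result. The article places ANCOVA on baseline tests, where it is of little use. Its text on the treatment effect, followed as written, gives a valid change-score comparison that is less precise than ANCOVA. That comparison meets the stated 80% power if 9.9 is the SD of the change; if 9.9 is the SD of the score, it does so only when r is 0.5 or more.

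For assumed r of 0.3 to 0.7, adjusting for baseline gives about 84 to 98% power if 9.9 is the score SD, or 93 down to 86% if it is the change SD. Half-widths are 3.46 to 4.63 points against 4.85. The stratum's own contribution is small, about 1 to 4 power points for an assumed 2 to 10% of variance.

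That baseline tests are of little use after randomisation is firm. The size of the precision gain is less so, because it rests on values the article does not give.

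**What to change.** In the Analysis section:

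- State the primary analysis as ANCOVA of week-6 K-ADHD-RS on randomised group, with baseline K-ADHD-RS (continuous) and medication stratum (envelope series 1-60 versus D1-D40) as covariates, reporting the adjusted difference and its 95% interval. Using the change as the response gives the same treatment estimate once baseline is a covariate.
- Use the same model for continuous secondary outcomes that have a baseline measurement.
- Keep the analyses within strata, labelled as secondary.
- Replace the baseline significance tests with a descriptive table by group.

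In the Sample size justification, say whether 9.9 is the SD of the score or of the change.

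The cost is a few sentences. It needs no new data, no more participants and no other software: baseline score and stratum are already recorded, and SPSS fits the model. Fixing the model before the data are seen also prevents a later choice among raw, change and adjusted estimates. That matters in an open trial whose Discussion acknowledges an unblinded assessor.

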## Abstract

**Background:**

Attention-deficit/hyperactivity disorder (ADHD) is a common neuro-psychiatric problem, affecting 7-9% of children. Pharmacological interventions are widely used with behavioral treatments in ADHD. Still, the origin of ADHD is unclear, limiting pharmacological effectiveness and making adverse effects common. The use of complementary and alternative medicine (CAM) has increased, especially for developmental and behavioral disorders, such as ADHD. CAM is used by 60-65% of parents of children with ADHD to relieve ADHD-associated symptoms and to avoid the side effects of conventional medication. Acupuncture has been widely used to treat patients with ADHD, but the available evidence of its effectiveness is insufficient. Our aim was to evaluate the effectiveness and safety of acupuncture in patients (both and each treatment naive and conventional therapy children) with ADHD (any subtype) compared to the waitlist control.

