## Methods/Design

### Design

A 6-week, randomised, waitlist controlled trial of acupuncture for the treatment of ADHD in children/adolescents is being conducted at Kyung-Hee Oriental Medical center, Seoul, Korea. All screening appointments and study visits occur in the neuropsychiatry clinic for outpatients. This study was ethically approved by the Kyung-Hee Korean Medical Center Institutional Review Board, and was registered with the Clinical Research Information Service (CRiS) (KCT0000019) as a waitlist controlled, randomised clinical trial. This study had two parallel arms (acupuncture and waitlist group) with a 1:1 patient allocation ratio (40 participants per arm).

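### The subgroups called treatment naive and conventional therapy are the drug strata under inaccurate names, and the sample size does not support an answer in each of them

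*Protocol article*

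**What the plan says.** **Strata.** In the protocol article, Randomization and treatment allocation, randomisation is carried out separately "within each of two subsets of participants (without pharmacologic intervention, 1-60; with pharmacologic intervention, D1-D40. Other treatments were not concerned".

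**Subgroups.** The Analysis section runs every analysis "performed among two randomised (acupuncture, and waitlist) groups and their stratified (treatment naive, and conventional therapy) sub-groups". The Background paragraph of the abstract sets the aim as effectiveness and safety in "both and each treatment naive and conventional therapy children".

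**Who may enter.** The Participants section accepts children on any kind of ADHD intervention, drug or non-drug, if nothing changed in the previous two weeks. The Discussion expects existing regimens that are drug, psychosocial or both, as well as children with no earlier therapy.

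**Sample size.** Sample size justification states: "This study is powered to detect a 7.04 difference between the groups", "assuming an equivalent standard deviation of 9.9 in both groups". It continues: "A sample size of 32 per group is required to achieve 80% power with a 2-tailed significance level of .05". After dropout: "Estimating a 20% dropout during the study, a minimum of 80 total participants are needed to reach the target 32 participants per group". No size or power is given for either stratum.

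**The concern.** Two things do not fit together.

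First, the names do not describe the strata. A child on behavioural therapy without a drug takes an envelope from the 1-60 series. So does a child who stopped a drug more than two weeks before entry. Neither is treatment naive. The closing paragraph of the Discussion itself counts psychosocial treatment as conventional, so by the article's own usage the first child would belong under conventional therapy. An effect reported for treatment-naive children would come from a group of unknown composition.

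Second, the abstract promises an answer in each subgroup and the Analysis section repeats every analysis within each, while the trial is sized only for the two arms as a whole. With low power in both strata, a significant result in one and not in the other is a likely chance pattern even when the effect is the same, and it is easily misread as a difference in effect.

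**Working it through.** **1. The definitions side by side**

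| Child at entry | Stratum (Randomization) | Literal meaning of the Analysis labels |
|---|---|---|
| On a drug | with drug (D1-D40) | conventional therapy |
| No drug, on psychosocial or occupational therapy | without drug (1-60) | not treatment naive |
| No drug now, drug in the past | without drug (1-60) | not treatment naive |
| Never treated | without drug (1-60) | treatment naive |

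The middle two rows are eligible and break the match.

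**2. The protocol's own sample size**

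Inputs from Sample size justification: difference 7.04, SD 9.9, two-sided 0.05, power 80%, dropout 20%.

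- n per group = 2 × [9.9 × (1.960 + 0.842) / 7.04]² = 31.04, rounded up to 32.
- Power of the two-sample t-test at 32 per group = 80.0%.
- 32 / 0.8 = 40 per group, 80 in total.

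The stated figures reproduce. All 64 completers are needed to reach 80%.

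**3. Power within one stratum**

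The split between strata is not stated. With 80 children, the envelope numbers allow 40 to 60 off drug and 20 to 40 on drug. Assumptions: 20% dropout in each stratum, equal arms, and the same difference and SD in both strata. The test is a two-sample t-test with n completers per arm and noncentrality 7.04 / (9.9 × √(2/n)).

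| Split of the 80 (off / on drug) | Completers per arm | Power off drug | Power on drug |
|---|---|---|---|
| 40 / 40 | 16 / 16 | 49.5% | 49.5% |
| 48 / 32 (60:40, ratio of the envelope series) | 19.2 / 12.8 | 57% | 41% |
| 60 / 20 | 24 / 8 | 67% | 26% |

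The difference detectable with 80% power at 60:40 is 9.2 points off drug and 11.4 points on drug, against 7.04 in the plan.

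**4. Chance of a split result when the effect is 7.04 in both strata**

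The chance that exactly one stratum is significant is p₁(1 − p₂) + p₂(1 − p₁).

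- Equal split: 2 × 0.495 × 0.505 = 50%.
- 60:40: 0.573 × 0.593 + 0.407 × 0.427 = 51%.
- 60/20: 0.674 × 0.737 + 0.263 × 0.326 = 58%.

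The chance that both are significant is 24%, 23% and 18% respectively.

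**5. Precision of a direct comparison of the strata**

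The standard error of the difference in effects is 9.9 × √(2/n₁ + 2/n₂): 4.95 at the equal split, 5.05 at 60:40 and 5.72 at 60/20. The 95% interval is about ± 9.7 (1.96 × 4.95) to ± 11.2 points (1.96 × 5.72). Power to detect a 7.04-point difference in effect is about 23% to 30%.

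**6. Size needed for 80% in each stratum**

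32 completers per arm per stratum: 4 × 32 = 128 completers, or 128 / 0.8 = 160 randomised.

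**The case against.** A reader might infer that the trial will analyse subgroups other than those it randomised within. The text does not support that. The Analysis section calls them stratified subgroups, drug treatment is the only stratification factor in the article, and no second classification of children is described. The natural reading is that the drug strata are analysed under loose names. The fault is in the labels, not in the set of children analysed.

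A reader might also infer that the protocol claims 80% power in each stratum. It does not. The sample size section speaks only of the two groups. The aim in each subgroup appears only in the abstract; the Objectives section and the Discussion's closing question leave it out. Underpowered subgroup analyses beside an adequately sized main comparison are common.

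The 57% and 41% are not protocol figures. There are 100 envelopes for 80 children, so 60 and 40 are capacities and not an expected ratio. The calculation also counts completers only, while an intention-to-treat analysis is planned for K-ADHD-RS. If all 80 children contributed full information, power at 60:40 (24 and 16 per arm) would be 67% and 49%, and the most either stratum could reach under any allowed split is 77% off drug (30 per arm) and 59% on drug (20 per arm). That is still short of 80%.

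Finally, an interaction model and an exploratory label are details that an article may leave to the analysis plan. Their absence is not held against the article. They are offered as the remedy.

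All of this narrows the point. What stands is that the labels are inaccurate for the no-drug stratum, and that the abstract's aim in each subgroup has no sample size behind it.

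**Conclusion.** The point holds in this form. The abstract and the Analysis section name the randomised strata in a way that their definition does not support, and a statement about treatment-naive children would be wrong as long as the no-drug stratum includes children on other therapy or with earlier drug treatment. How many such children there are cannot be known from the article.

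The aim of an answer in each subgroup is not backed by the sample size. Power within a stratum runs from about 26% to 67% over the splits that the envelopes allow, assuming 20% dropout and the same difference and SD in both strata. The exact figure depends on the split; the conclusion that neither stratum reaches 80% does not. The overall comparison is unaffected. This should be corrected, but it does not threaten the primary result.

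**What to change.** 1. Define the subgroups as without and with pharmacologic treatment at randomisation, identified by envelope series 1-60 and D1-D40. Drop the term treatment naive from the abstract and the Analysis section, and replace conventional therapy to match.
2. Estimate the stratum effects from one model with a group-by-stratum interaction. Report each stratum estimate and the interaction with 95% confidence intervals, labelled exploratory.
3. State that the 80% power applies to the whole randomised population only, and bring the abstract's aim into line with the Objectives section.

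The cost is some wording and one model term, with no extra children or data. The subgroup claims become weaker. The interaction estimate will be imprecise, so it guards against misreading a split result but does not settle whether the effect differs. If an answer in each stratum is truly wanted, the alternative is to size each one, at about 160 randomised instead of 80.

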## Discussion

We have a presented the design and the protocol for the randomised controlled trial of acupuncture for childhood ADHD. The participants of this study will have acupuncture added to their existing medical regimen (pharmacologic and/or psychosocial) or no previous therapy at all, and will be monitored for changes in their outcomes (i.e. inattention, hyperactivity and impulsivity) in the short-term (3 and 6 weeks) and during a 9 week follow-up. Completion of this trial will help provide the answer to the question "Does acupuncture have a role to play in the management of children with ADHD?" Results of this trial will be disseminated at the completion of the study.

This is the first acupuncture trial protocol study in ADHD. Case studies of acupuncture effects for ADHD already exist, especially in China, but trial protocols are not precisely described. Our protocol will help to make better quality acupuncture studies for ADHD. Furthermore, we tried to gather objective measurements using CNT40. Subjective measurements, like K-ADHD-RS in this study, are commonly used in ADHD and have adequate reliability and validity. But lack of objective measurements in ADHD may lead to some disputes like parental placebo effects.

In traditional Korean medical theories, the insufficiency of yin, results in an excess of yang. The imbalanced condition of the whole body leads to impaired mental symptoms like attention deficit, hyperactivity and impulsivity. Thirteen acupuncture points have been chosen in this context. The acupuncture points located on the head region takes a main role for controlling the spirit. Qi of five viscera and six bowels belong to the head region. For balance of the whole mind and body, acupuncture points in the head region are essential. Baihui (GV20), Sishencong (EX-HN1) are representative points for the head region. Quchi (LI11) takes a role in the elimination of excessive yang and Sanyinjiao (SP6) supplements insufficient yin. It yields a better mental balance. Hegu (LI4), Taichong (LR3) assists in harmonious circulating qi and blood.

One limitation of this study involves the waitlist for the controlled group. Many researchers commonly prefer placebo controlled designs to the waitlist ones in randomised control trials. Placebo effects of acupuncture were actively studied in many articles and sham acupuncture is a representative method for an acupuncture placebo tool. But there is a lack of consensus on the most valid approach to establishing an acupuncture placebo. So, important aspects of the placebo acupuncture control need to be considered. "Inert" is the main topic in placebo acupuncture control. Placebo acupuncture strategies mainly consist of superficial (or minimal) insertion, non-acupuncture insertion points insertion, and sham acupuncture. But each approach has some defects. First, a superficial (or minimal) insertion is not a real placebo method because it induces peripheral sensory stimulation. It does not seem possible to insert acupuncture needles without any sensory stimulation [64,65]. In fact, even a very mild form of placebo acupuncture seems to exert an effect [66]. Second, non-acupuncture insertion points may not be inert. Needling in the areas around the traditional acupuncture points may be equally efficient [66]. Acupuncture areas or zones are understood to be like acupuncture points in the current ongoing discussion. Third, some articles have suggested that sham acupuncture may not be inert [67,68]. Re-examination of acupuncture trials is needed, to ascertain whether a sham that was assumed to be inert was in fact not inert [67]. In this context, a placebo acupuncture, as a control intervention, is not adequate enough to observe acupuncture effects. Although waitlist is an imperfect control method as well, we used it to observe definite acupuncture effects in ADHD.

Not separating assessor from randomization is an additional limitation. Every measurement was assessed by the person who conducted the screening phase, so as not to be blinded from randomization. Although we tried to maintain an objective standpoint, we could not exclude observer bias, which all researchers brought to their work and which helped to determine their method of research and their observations. To minimize this bias, we involved objective ADHD measurement tools, like CNT40 and FAIR.

Finally, a paper case record form (CRF) was used in this study. These days, electronic case record form (e-CRF) system, like the Clinical Data Interchange Standards Consortium (CDISC) e-CRF, is become preferred because of its improved quality and efficiency in trial study. In July 2010, the Korea CDISC Coordination Committee (K3C) started making standard e-CRF forms, but we used paper CRF instead, due to insufficient e-CRF infrastructure. Paper CRF may lead to data loss and input errors. The Kyung-Hee Korean Medical Center Institutional Review Board strictly supervised data storage and management. We also reexamined the inputted data.

Subjective measurements, like K-ADHD-RS, are commonly used in ADHD, and have the best evidence. Although these measurements have adequate reliability and validity, lack of objective assessment in ADHD may lead to some disputes, like parental placebo effects. More objective measurements, like the presently used CNT40, have to be validated in ADHD trials. Furthermore, as an evidence-based treatment in ADHD, acupuncture has little evidences compared with conventional pharmacological or psychosocial treatment. This study will give some evidence for the effectiveness of acupuncture as an add-on treatment in treating children with ADHD.

